#### Subgroup analysis

Based on a previous trial showing that benefits from 33°C TTM in cardiac arrest were greatest in the subgroups of patients with long no-flow times and low-flow times (most notably longer than 15 minutes) [74-76], we plan to perform analyses in these two subgroups.We will also analyze other subgroups defined based on the following prognostic factors: presence of a witness (yes/no); in-hospital versus out-of-hospital cardiac arrest; and probable cardiac origin (yes/no), which was a stratification variable.Finally, to take the baseline cerebral performance category into account, we will compare subgroups with CPC1-2 versus CPC 3–4 before randomization.

## Methods: monitoring

### Data monitoring

The results of the interim analysis will be provided to the Data and Safety Monitoring Board (DSMB), which will make recommendations about whether to continue or stop the trial. The DSMB is composed of 3 physicians not otherwise involved in the trial. For both interim analyses, the DSMB will have access to unblinded results on day-90 CPC, day-90 mortality, and secondary safety outcomes (dialysis, infection, and seizure event). The results of the interim analysis will not be disclosed unless they lead the DSMB to request premature trial discontinuation. The DSMB members are [name] [name] (Department of Critical Care Medicine, Cliniques Universitaires Saint Luc, Université Catholique de Louvain, [name]), [name] (Medical ICU, Saint-Antoine Teaching Hospital, Assistance Publique-Hôpitaux de Paris, [name]), and [name] (Medical ICU, Lariboisière Teaching Hospital, Paris-Diderot University, Paris, France).

### Harms

The trial may be temporarily stopped for an individual patient, at the discretion of the attending physician, in case of major serious adverse events suspected to be associated with the type of temperature management. According to French law, as the strategies used in both study arms are classified as standard care, no specific reporting procedure for unexpected serious adverse events is planned. Follow-up data on expected serious adverse events are recorded in the eCRF; these events may include bleeding, cardiogenic pulmonary edema, renal replacement therapy, infection, and withholding or withdrawing of life-sustaining treatments.

## Ethics and dissemination

### Research ethics approval

The trial is conducted in compliance with the current version of the Helsinki Declaration and good clinical practice guidelines. The research project was approved by the ethics committee of the French Intensive Care Society (SRLF) on October 6, 2011, and by the appropriate Ethics Committee for the Protection of Patients (CPP Ouest 2) in Angers, France, on June 11, 2013.

### Consent or assent

According to French law, because the strategies used in both study groups are considered components of standard care, there is no requirement for *consent*. Instead, *information* of the patients or next of kin is required. All patients assessed for enrolment in the trial are comatose and therefore unable to understand information. Their next of kin is informed about the trial and confirms in writing that he/she has received this information. If no next of kin can be contacted during screening for the study, trial inclusion is conducted as an emergency procedure by the ICU physician, in compliance with French law. Patients who regain consciousness are informed about the trial as soon as possible and asked for written confirmation that they received this information.

A patient may withdraw from the trial at any time if the person informed about the study (patient or next of kin) is unwilling to continue in the trial. The person requesting trial withdrawal is asked for permission to continue data recording and to perform the part of the day-90 telephone interview consisting in a semi-structured CPC assessment; patients who accept this partial withdrawal modality have their data kept in the study analyses. Patients who request full withdrawal have all their data deleted.

Patients transferred to another ICU are withdrawn from the trial if the transfer occurs before the end of the TTM phase, unless the new ICU is participating in the trial, in which case the patient is kept in the same treatment group. All patients transferred to another ICU are followed for determination of the primary endpoint.

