### Blinding

Blinding of healthcare workers, patients (despite the sedation), and families to the type of temperature management is not feasible. However, the primary outcome is assessed by a psychologist blinded to the treatment arm, during a semi-structured telephone interview [62].

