### Statistical methods

#### Statistical analysis

A predefined statistical analysis plan will be followed. The intention-to-treat principle will be applied. The statistical report will incorporate the data recommended by the CONSORT Statement extension for nonpharmacologic treatment interventions [72].

Descriptive statistics will be used to compare the two randomization groups, without statistical testing. The chi-squared test will be performed to compare the primary endpoint in the two groups. Two interim analyses will be conducted, after the inclusion of 200 and 400 patients, respectively. The rule developed by Peto and Haybittle [73] will be applied, with the significance level set at 0.001 for both interim analyses and the significance level associated with the final analysis set at 0.049 to maintain an overall Type I error of 5%.

Secondary endpoints evaluating binary variables (need for renal replacement therapy, acute cardiogenic pulmonary edema, and binary day-90 neurological outcome) will be compared using the chi-squared test. Secondary endpoints evaluating quantitative variables (biological tests, stay lengths, and mechanical ventilation duration) will be compared using the Student t test or Mann–Whitney test.

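### Intention-to-treat is promised without exception, yet full withdrawals are deleted after randomization, and the analysis status of early-transferred patients is left unclear

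*Protocol article*

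**What the plan says.** All of this is in the protocol article.

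- **Statistical analysis:** "The intention-to-treat principle will be applied". No exception is attached.
- **Consent or assent, who may withdraw:** "A patient may withdraw from the trial at any time if the person informed about the study (patient or next of kin) is unwilling" to go on. Next of kin are informed at enrolment if they can be reached; otherwise inclusion is an emergency procedure. "Patients who regain consciousness are informed about the trial as soon as possible".
- **Consent or assent, two kinds of withdrawal:** the person withdrawing is asked to allow continued data recording and the day-90 CPC part of the interview, and "patients who accept this partial withdrawal modality have their data kept in the study analyses". For the rest, "Patients who request full withdrawal have all their data deleted".
- **Consent or assent, transfers:** "Patients transferred to another ICU are withdrawn from the trial if the transfer occurs before the end of the TTM phase", unless the receiving ICU takes part in the trial. The paragraph then ends: "All patients transferred to another ICU are followed for determination of the primary endpoint".
- **Blinding:** "Blinding of healthcare workers, patients (despite the sedation), and families to the type of temperature management is not feasible".

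**The concern.** A randomized patient whose data are deleted leaves both the numerator and the denominator of the primary chi-squared test. That cannot be squared with an unqualified intention-to-treat statement. Nor can the unseen analysis plan repair it, since the article itself fixes the deletion rule and a deleted outcome cannot be recovered. Only a count by arm can be kept, and that has to be arranged in advance.

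What is at stake is bias more than power. Everyone is comatose at enrolment, so a patient can refuse in person only after waking, and a patient must wake to reach CPC 1 or 2. Patients and families also know the arm. Deletions could therefore depend on both outcome and arm.

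The transfer wording raises a smaller question. The article does not define what being withdrawn from the trial means, and it uses the term directly after a rule that deletes the data of some withdrawn patients. A reader cannot tell whether these patients stop only the trial's procedures or also leave the analysis set, nor what becomes of their secondary and safety outcomes.

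**Working it through.** **Inputs from the article.** CPC 1-2 at day 90: 14% in control and 14% + 9% = 23% with hypothermia; 80% power; two-sided 5%; 292 per group (Sample size). Final significance level 0.049 and chi-squared test (Statistical analysis). Allocation 1:1 (Allocation). No withdrawal rate is given, so every number of deletions below is an assumption.

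**1. The plan's own figure.** Pooled two-proportion formula with mean rate 0.185:

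n = [1.960 × √(2 × 0.185 × 0.815) + 0.842 × √(0.14 × 0.86 + 0.23 × 0.77)]² / 0.09² = 291.02, rounded up to 292 per group, 584 in all.

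This matches exactly, so 584 contains no allowance for deleted patients. At 0.049 the formula gives 292.8, or 293 per group.

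**2. Deletion unrelated to outcome.** Exact binomial power of the uncorrected chi-squared test at 0.049, 14% against 23%:

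| Analysed per arm | Assumed loss | Power |
|---|---|---|
| 292 | 0% | 80.2% |
| 283 | 3% | 78.9% |
| 277 | 5% | 78.1% |

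The cost is 1 to 2 points.

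**3. Assumed worst case under no true effect.** Both arms have 292 patients and a true rate of 14%. In one arm only, k patients, all CPC 1-2, are deleted. The expected rate left in that arm is (0.14 × 292 − k) / (292 − k), with 0.14 × 292 = 40.88. The type I error is summed over both binomial distributions.

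| k deleted | Expected rate left | Spurious difference | Type I error at 0.049 |
|---|---|---|---|
| 0 | 14.0% | 0 | 4.9% |
| 3 | 37.88/289 = 13.1% | 0.9 points | 6.4% |
| 6 | 34.88/286 = 12.2% | 1.8 points | 10.7% |
| 9 | 31.88/283 = 11.3% | 2.7 points | 18.0% |

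Nine deletions are 9/292 = 3.1% of one arm. The sign of the error depends on the arm: deletions in the control arm favour hypothermia, and deletions in the hypothermia arm count against it.

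If the deleted patients are instead all CPC 3-5, little happens. By normal approximation, losing 1% to 5% of one arm shifts the difference by 0.1 to 0.7 points and gives a type I error of 4.9% to 5.6%.

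**4. What it takes to change a result.** Pearson chi-squared without correction, good-outcome hypothermia patients deleted:

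- At the planned rates (0.14 × 292 ≈ 41, 0.23 × 292 ≈ 67): 41/292 against 67/292, p = 0.0056. Three deletions (64/289) give p = 0.011. Nine (58/283) give p = 0.040. Ten (57/282) give p = 0.0495, the first value above 0.049.
- At the threshold: 41/292 against 59/292, p = 0.048. One deletion (58/291) gives p = 0.058. One deletion of a good outcome from each arm (40/291 against 58/291) gives p = 0.046.

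**5. The transfer sentences side by side.** The first takes patients who move before the end of the TTM phase to a non-participating ICU out of the trial. The second follows every transferred patient for the primary endpoint. No sentence deletes their data or excludes them from analysis, and none states how they are analysed.

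**The case against.** The strongest reply has four parts.

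- **Partial withdrawal protects the primary endpoint.** Deletion is what remains after the person has been asked to allow data collection and the CPC interview. This is right and limits the numbers. It does not reconcile the two statements for those who decline.
- **The link to outcome is not shown.** Next of kin can withdraw patients who stay comatose, and a conscious patient may still be CPC 3. This stands. A reader might infer that deletions systematically remove good outcomes, but the article supports only that they could.
- **The p-value illustration is chosen at the threshold.** A reader might infer that the result can hinge on one or two deletions. That is true of any result lying on the threshold: with no deletion at all, one event fewer (58/292) gives p = 0.061. At the planned effect, ten deletions in one arm are needed.
- **Transferred patients are not lost.** A reader might infer that early transfers leave the randomized comparison or that their secondary and safety data are discarded. The article says neither. It follows all of them for the primary endpoint, and the deletion rule covers only those who request full withdrawal. Only the undefined term remains at issue.

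It can also be said that analysis sets and sensitivity analyses belong in the analysis plan, which is not shown. That would answer a complaint about missing detail. Here two stated rules conflict.

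**Conclusion.** The point holds in a limited form. With full withdrawals deleted, the primary analysis covers all randomized patients except those, and should not be called intention-to-treat without qualification.

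The effect on power is negligible at any plausible low rate of random loss. The effect on bias is unknown in size and direction. The 6.4%, 10.7% and 18% are ceilings that assume every deleted patient had a good outcome and all came from one arm; they are not forecasts. They do show that a one-sided loss of about 3% of an arm would be enough to matter, which is why the counts by arm need to be kept.

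For early transfers the finding is an ambiguity to be reconciled, not an exclusion.

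**What to change.** - **Population statement.** In the statistical section, define the primary population as all randomized patients, analysed in the arm assigned, except full withdrawals whose data must be deleted.
- **Counts.** Keep the non-identifying number of full withdrawals by arm from the randomization list and report it in the patient flow.
- **Sensitivity analyses.** Repeat the primary test with these patients back in the denominators: best case (hypothermia withdrawals counted as CPC 1-2, control withdrawals as CPC 3-5), worst case (the reverse), and a tipping-point table over the assignments in between.
- **Transfers.** Reconcile the two sentences by stating that transferred patients stay in the analysis as randomized, for the primary endpoint and for every other outcome that can be obtained.

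The cost is a few sentences, one extra sensitivity table, and a less favourable label than intention-to-treat. The right to deletion is respected, because only counts are kept. With 161 of 584 patients included by February 2, 2015, the change could still be made during enrolment.

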### Confidentiality

The study data will be handled as requested by the French Data Protection Authority (Commission Nationale de l’Informatique et des Libertés). All original records will be kept on file at the trial sites or the coordinating data managing center for 15 years. The clean electronic trial database file will be anonymized and kept on file for 15 years.

## Discussion

Few data are available to explain the discrepancies among the findings from trials of TTM, most notably in patients with nonshockable cardiac arrest. The beneficial effects of 32.5°-33.5° TTM probably vary with the degree of brain damage at treatment initiation. The ischemic penumbra concept developed for stroke is probably applicable to the brain damage seen after cardiac arrest. In a study of patients with nonshockable cardiac arrest, the benefits from 32.5°-33.5° TTM were greatest when the no-flow time was longer than 8 minutes [76]. Similarly, in another study of patients with shockable or nonshockable cardiac arrest, 32.5°-33.5° TTM was most effective in the subgroup whose time from cardiac arrest to the return of spontaneous circulation (ROSC) was longer than 15 minutes [74]. In a previous pilot study, 32° was better than 34° as the target temperature [77]. The TTM Trial published in *The New England Journal Medicine* [19] showed that TTM at 36°C was similar to TTM at 33°C in patients with good prognostic factors including witnessed cardiac arrest in shockable rhythm with short no-flow and low-flow times compared to patients enrolled in earlier trials and having less favorable prognostic characteristics [7,8]. Figure 3 reports the estimated benefits of TTM and Figure 4 the effects documented in previous studies and the expected effects in the HYPERION trial.

**Figure 3 Fig3:**
[figure not shown]
**Benefits from targeted temperature management in relation to patient’s prognosis.**

**Figure 4 Fig4:**
[figure not shown]
**Benefits from targeted temperature management in relation to patient’s prognosis documented in previous studies and expected in the HYPERION trial.**

Our decision to use a 24-h period of normothermia after 32.5°-33.5° TTM was based on reports that rebound hyperthermia adversely affected the outcomes of patients with cardiac arrest [42,78]. Whether rebound hyperthermia is a causal or an associated factor for mortality or neurological outcome after 32.5°-33.5° TTM is unclear. However, the TTM Trial [19] established the importance of preventing hyperthermia after cardiac arrest.

In conclusion, the HYPERION trial is the first registered randomized controlled trial evaluating the potential benefits of 32.5°-33.5° TTM on the neurological outcome of patients after nonshockable cardiac arrest.

## Abbreviations

BSAS: Bedside shivering assessment scale
CPC: Cerebral performance category
eCRF: Electronic case-report form
ICU: Intensive care unit
ROSC: Return of spontaneous circulation
TTM: Targeted temperature management
